### Standard diet intervention for weight loss

Both study groups will receive the same standard diet intervention for weight loss following the primary health care guidelines [25]. They will see a primary health care professional every 2 weeks during the first 3 months, and monthly thereafter. The visits will take place in the offices of primary care doctors and nurses. The main objective of the usual diet intervention for weight loss is to change dietary paterns, rather than focus on changing specific food choices. The intervention is designed to be carried out during a 12-month period, with 15 total visits. The first visit lasts one hour and followed by 15-min monthly visits. Each visit address one item that is characteristic of a balanced diet, using educational materials specifically designed for the intervention. Use of these supporting materials helps to reeducate patients about dietary intakes as health professionals individualize the messages based on each person’s specific dietary habits.

### Experimental group

The experimental group will receive the standard diet intervention for weight loss plus free Smartphone app plus a wearable device. ***Description of the mobile app***: The app to be tested in the present trial has three distinct functions: (a) Self-monitoring of food intake, recorded to help determine the quantity of calories consumed each day, and physical activity, used to establish a calorie plan adapted to the profile and daily activities of each participant. The calorie target zone is automatically adjusted, depending on the individual’s activity throughout the day; (b) Social networking, which makes it easy to share experiences and allows comparison of statistical data (and competition!) with other users, sharing successes and encouraging each other; the classification chart is continuously updated throughout the day; ***Description of the wearable device***, a bracelet synchronized with the app, that delivers real-time physical activity statistics “to the wrist and to the app”. The device poses daily challenges in terms of steps per day or distance per activity session. It also monitors hours of sleep and sleep quality.

### Control group

Participants in the control group will only receive standard diet intervention for weight loss.

### Training for participating health professionals

To ensure the fidelity of the standard diet intervention, health professionals will participate in 8 h of targeted training to review the theoretical concepts supporting the protocol. The training will be presented by the research team’s experts in nutrition, with the goal of reviewing and standardizing the messages to study participants to improve the homogeneity of the intervention.

### Pilot test

We will perform a pilot study with 15 participants in each group.

### Data collection

#### Demographics and medical history

During **visit 1 (baseline)** and **visit 14 (end of follow-up)**, an interviewer-guided survey will be completed by the patient and primary care nurse or doctor and blood tests will be ordered. The following data will be obtained: (a) Sociodemographics– sex, birthdate, educational level, profession and social rank, categorized using the National Classification of Occupations (*Clasificación Nacional de Ocupaciones* [CNO-2011]); (b) History of diseases and use of toxic substances – tobacco and number of cigarettes smoked per day, amount (gr) of alcohol consumed per week, other toxic substances, and usual medication; and (c) Blood test: complete blood count, renal function, liver function, lipid profile, glycaemia.

#### Physical examination

At each study visit, anthropometrics will be recorded by a primary care nurse or doctor. Body weight will be measured with the participant dressed in light clothing with shoes off on a calibrated balance. Waist circumference will be measured (to the nearest 0.5 cm) following a normal exhalation at the mid-point between the twelfth rib and superior border of the iliac crest. The average of the last two of three measures will be used to determine resting blood pressure, measured with an automated device (Omron HEM 907) in the supine position following a 5-min rest.

#### Dietary history and physical activity

At baseline (visit 1) and at end of follow-up (visit 14) the nurse will register food intake using two methods, a validated food frequency questionnaire [26] and 24-h recall, to arrive at an average daily energy consumption estimate (in calories) and determine an individualized dietary pattern. At baseline (visit 1), and at visits 3, 6, and 12 months (end of follow-up), physical activity will be measured with two brief validated questionnaires [27], administered in the participant’s preferred language (Catalan or Spanish).

Moreover, all participants will encouraged to self-record their food intake, using the Smartphone in the experimental group and a traditional paper-based food diary in the control group. These records will be reviewed by a nurse at baseline, at 6 and 12 months.

#### Process measures

We will determine the retention rates by attendance at follow-up visits. In the experimental group, we will monitor the average number of entries per week for diet and physical activity to observe patterns of use.

In addition, we will carry out in-depth interviews with a subsample of participants as they complete the study to determine acceptance and satisfaction related to the Smartphone application, standard diet intervention and the combination of standard diet intervention with the app. We will ask an open-ended question about the app’s ease of use.

### Outcomes

The **primary outcome** will be change in body weight at 3, 6 and 12 months in the experimental group, compared with the control group.

**Secondary outcomes**, comparing the intervention group to the control group, will be four-fold: (a) changes in BMI, waist circumference, and physical activity at 3, 6 and 12 months; (b) changes in cardiometabolic risk factors such as systolic blood pressure, glucose, total-cholesterol, LDL-cholesterol, and HDL-cholesterol at 12 months; (c) change in GPT at 12 months; and (d) change in dietary pattern at 12 months.

**Tertiary outcomes** will be related to adherence and satisfaction: (a) adherence to the intervention, measured by (a1) difference in follow-up visits attended, compared to possible total, in both groups and (a2) difference in mean number of days of self-reported diet entries between groups; (b) frequency of using the app and wearable device; (c) satisfaction with Smartphone app and with standard diet intervention.

### Statistical analysis

Analysis will be based on intention to treat. Basal analysis will determine the comparability of the two study groups according to the study variables. Quantitative variables with a normal distribution will be described as means and standard deviation, or median and interquartile range otherwise, and qualitative variables as percentages and 95 % confidence intervals. Quantitative basal characteristics will be compared using Student *t* test and qualitative variables using Pearson chi-square test.

A hierarchical linear model (HLM) will be used for longitudinal data, presented as a 2-level hierarchical structure: level-1 units consist of the repeated measures for each subject, and level-2 units will be the subject. HLM allows the estimation of inter-individual differences in intra-individual change over time by modelling the variances and co-variances. All covariables that are significant at *p* < 0.30 in bivariate analysis will be included in the model. This strategy will sufficiently reduce the probability of leaving relevant variables out of the model.

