#### Participants and settings

Participants (*n* = 70) will be recruited from two primary healthcare centres in the city of Tarragona and surrounding areas and randomly assigned to a standard diet intervention (**control group**, n = 35) or standard diet intervention plus a free Smartphone application and wearable device (**experimental group**, *n* = 35). A personalized letter will be sent to the attention of the centre administrators, requesting collaboration and providing a copy of the study protocol. Within 2 weeks, the administrators will be contacted by telephone to confirm their participation.

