### Sample size

Accepting an alpha risk of 0.05 and a beta risk of 0.2 in a two-sided test, **70** subjects are necessary in each group, with an estimated 30 % loss to follow-up, to recognize as statistically significant a difference greater than or equal to 3.9 kg [22]. The common standard deviation is assumed to be 4.826 kg.

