## Discussion

One of the study limitations is its open design. It is impossible to mask the intervention; both patients and health professionals in the experimental and control groups will be aware that they are participating in a weight loss intervention, which could affect the success or failure of the intervention and has the potential to introduce bias. Randomization of patients to study groups will help to achieve a balance in sociodemographic and anthropometric characteristics, as well as risk factor profile. Potential confounding factors will be controlled by applying the appropriate multivariate analysis. The researcher responsible for the statistical analysis will be blinded to study group assignments.

Although the study results cannot be applied to all health-related mobile apps, limiting the external validity of the study, they will likely be generalizable to apps with characteristics similar to this free app. Another possible limitation is the length of the study period. One of the great challenges to patients who have lost weight is to maintain the weight loss longer than a year. Based on the study results, however, follow-up strategies will be designed to support participants beyond the end of the study period within the framework of the universal primary care system in Catalonia.

Among the strengths of the study is that this clinical trial has the potential to provide a validated weight loss tool that could be very useful to patients accessing primary health care who want to lose weight. Very few studies to date have validated the effectiveness of weight loss apps, and none of them were done in our setting.

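### Baseline significance tests cannot settle comparability of randomised groups, and the plan does not fix baseline weight in the primary model

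*Protocol article*

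**What the plan says.** The Statistical analysis section of the protocol article plans an intention-to-treat analysis and a baseline comparison: "Basal analysis will determine the comparability of the two study groups according to the study variables". It plans descriptive summaries (mean and SD, or median and interquartile range; percentages with 95% confidence intervals) and then names the tests: "Quantitative basal characteristics will be compared using Student *t* test and qualitative variables using Pearson chi-square test". It gives no significance level for these tests, no measure of imbalance and no action that follows from the result.

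The primary analysis is a two-level hierarchical linear model, with repeated measures within subject. Covariates enter if they reach p < 0.30 in a bivariate analysis. The article does not say whether that analysis relates the covariate to the outcome or to the group. It names no covariate that is always included, and it does not say whether baseline weight is one of the repeated measures in the response.

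Patients are allocated individually and 1:1 (Screening and randomization). The Discussion relies on randomisation for balance and adds: "Potential confounding factors will be controlled by applying the appropriate multivariate analysis".

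**The concern.** In a trial with proper individual randomisation, any baseline difference between arms is due to chance. The null hypothesis of each baseline test is then true by design, and its p-value does not tell the reader whether the observed imbalance is large enough to disturb the weight comparison. That depends on the size of the imbalance and on how strongly the variable predicts weight change. The article asks the tests for an answer that they cannot give.

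Adjustment is the second part and the more important one. Baseline weight is collected on everyone and is an obvious candidate predictor of weight change. Under the stated rule, whether it is adjusted for can turn on a test result seen after the data are in. In a trial of about 70 patients, the estimated difference in weight change can depend somewhat on that choice.

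**Working it through.** **Inputs.** Two-sided 0.05 and power 80% ("Accepting an alpha risk of 0.05 and a beta risk of 0.2 in a two-sided test"), target difference 3.9 kg ("a difference greater than or equal to 3.9 kg"), SD 4.826 kg ("The common standard deviation is assumed to be 4.826 kg") and 30% loss ("with an estimated 30 % loss to follow-up"), all from Sample size. Participants and settings gives 35 per group; Sample size words it as 70 in each group. Using 0.05 for the baseline tests is an assumption, because the article sets no level for them.

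**1. Which group size the plan's inputs support.** n = 2 × (1.960 + 0.842)² × (4.826/3.9)² = 24.04 per group. Allowing for loss, 24.04/0.70 = 34.3, that is 35 per group and 70 in total. The inputs therefore reproduce 35 per group. Results for 70 per group are shown as well because the article prints that figure.

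**2. Largest observed difference that the t test leaves non-significant.** In SD units this is t(0.975, 2n − 2) × √(2/n).
- n = 35: 1.995 × √(2/35) = 1.995 × 0.2390 = 0.477 SD.
- n = 70: 1.977 × √(2/70) = 1.977 × 0.1690 = 0.334 SD.

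For a binary trait with 35 per group (Pearson chi-square, no continuity correction), 14/35 against 21/35, a gap of 20 percentage points, gives p = 0.094. A split of 13/35 against 22/35 gives p = 0.031.

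**3. The other direction.** Under correct randomisation each test is significant about 5% of the time. The chance of at least one p < 0.05 among k independent variables is 1 − 0.95^k: 40% for k = 10, 54% for k = 15, 64% for k = 20. The number of variables is an assumption, and correlation between them lowers these figures.

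**4. The p < 0.30 screen and baseline weight.** There are two possible readings of the bivariate analysis.
- *Screen on group differences.* Under correct randomisation the p-value is uniform, so P(p ≥ 0.30) = 1 − 0.30 = 0.70. Baseline weight stays out about 70% of the time. With 35 per group the entry threshold is t(0.85, 68) × √(2/35) = 1.044 × 0.2390 = 0.250 SD.
- *Screen on the outcome.* An observed correlation of 0.2 to 0.4 with weight change gives p = 0.097 to 0.0006 with 70 patients, and 0.168 to 0.004 with 49 completers (70 × 0.70). A predictor of that observed strength would enter.

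**5. Size of what the first reading leaves unadjusted.** Take the SD of weight change as 4.826 kg and the correlation r of baseline weight with weight change as 0.2 to 0.4 (assumption). An imbalance just under 0.250 SD shifts the contrast by r × 0.250 × 4.826 = 0.24 to 0.48 kg, or 6% to 12% of 3.9 kg. This is the upper end, since most excluded imbalances would be smaller.

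**The case against.** The case on the other side is strong on the p-values. A reader might infer that a non-significant baseline test will be taken as proof of equivalence, or a significant one as failed randomisation. The article says neither. It states no threshold, no equivalence reading and no consequence. The hierarchical model is not conditional on the tests. The planned descriptive summaries already let a reader judge the size of an imbalance. All of this stands.

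A reader might also put a 0.477 SD imbalance into kilograms: r × 0.477 × 4.826 = 0.46 to 0.92 kg for r = 0.2 to 0.4, or 12% to 24% of 3.9 kg. That shift belongs to an unadjusted contrast, which is not the planned analysis. With 35 per group, an imbalance of that size has p of about 0.05 and passes the 0.30 screen on the group reading. On the outcome reading, observed correlations of that size pass as well, although sampling variation could still let a predictor slip through.

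Nor does low power of the baseline tests help the argument. The chance of detecting a true 0.5 SD difference with 35 per group is 54%, but under randomisation there is no true difference to detect.

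Finally, a condensed article may leave model details to an analysis plan that is not shown, and baseline weight might be among the repeated measures. That is fair, and it limits the weight of the point. It does not remove it, because the article itself states a data-driven route for covariates and fixes none in advance.

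**Conclusion.** The point holds in a limited form. Baseline significance tests cannot determine whether randomised groups are comparable. With 35 per group at an assumed two-sided 0.05 level they leave observed differences up to 0.477 SD non-significant (0.334 SD with 70 per group). The effect of this alone is on how the baseline table is read, and dropping the tests would change no trial result.

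The part that can affect the result is that no prognostic baseline value is fixed in the primary model. On the group-difference reading of the screen, baseline weight would be left out about 70% of the time under correct randomisation. On the outcome reading it would usually enter if it predicts weight change at all well. The article does not say which reading applies. The consequence in kilograms is modest and rests on an assumed correlation. This is a free improvement, not a flaw that undermines the trial.

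**What to change.** In the Statistical analysis section:
- Delete the Student t and Pearson chi-square comparisons of baseline characteristics and the statement that the baseline analysis determines comparability.
- Present baseline values by arm with the summaries already planned, adding standardised differences if wanted.
- State that baseline weight is always in the primary hierarchical model, whatever the observed imbalance or screening p-value. It can enter either as part of the response vector with a common baseline mean in both arms, or as a covariate.

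The cost is a change of wording and the loss of the p-value column in the baseline table. No extra data or patients are needed.

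### For secondary outcomes measured only at baseline and 12 months, the planned HLM gives essentially a change-score contrast; prespecified baseline adjustment would be more precise for one degree of freedom

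*Protocol article*

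**What the plan says.** Under Statistical analysis, the protocol article gives a single model for outcomes: "A hierarchical linear model (HLM) will be used for longitudinal data, presented as a 2-level hierarchical structure". Level 1 holds each subject's repeated measures and level 2 is the subject. The reason given is that "HLM allows the estimation of inter-individual differences in intra-individual change over time by modelling the variances and co-variances". The t and chi-square tests in that section are for baseline characteristics only. Covariates enter by a screen: "All covariables that are significant at *p* < 0.30 in bivariate analysis will be included in the model". The section does not state the form of time, the random effects, or whether an outcome's baseline value is a response or a covariate.

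The measurement schedule differs by outcome:

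- **Blood tests.** Under Demographics and medical history, at visits 1 and 14, "an interviewer-guided survey will be completed by the patient and primary care nurse or doctor and blood tests will be ordered". The panel is "Blood test: complete blood count, renal function, liver function, lipid profile, glycaemia". I take liver function to include GPT.
- **Diet.** "At baseline (visit 1) and at end of follow-up (visit 14) the nurse will register food intake using two methods".
- **Outcomes section.** The secondary outcomes include changes in "glucose, total-cholesterol, LDL-cholesterol, and HDL-cholesterol at 12 months", and changes in GPT and dietary pattern at the same time point.

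Weight, BMI, waist and physical activity are outcomes at 3, 6 and 12 months, so they have at least four occasions with baseline. Systolic blood pressure is listed with the 12-month outcomes, but its measurement is described in the section on examinations at each visit. I do not count it among the two-occasion outcomes.

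**The concern.** The stated rationale, individual differences in change over time, suits outcomes with several measurements. Glucose, lipids, GPT and diet have two. For them the model reduces to a random intercept, and if baseline is one of the two level-1 responses, the group-by-time coefficient is in substance the between-arm difference in mean change.

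That estimator is valid in a randomised trial, but it does not use the fact that randomisation makes the baseline means equal in expectation. Models that do use it are at least as precise apart from a small degrees-of-freedom cost, and they need no new data. At stake is precision on a block of secondary outcomes in a small trial. A second issue is that, with adjustment left to a significance screen, whether a given outcome is baseline-adjusted is not fixed in advance and could differ between outcomes.

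**Working it through.** The documents state no figure on this point, so there is none to reproduce.

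**Inputs.** n = 35 per arm (Abstract; Participants and settings). Loss of about 30 % (Sample size), taken as 10 of 35 per arm, leaving c = 25. The baseline-to-12-month correlation rho is not given in the documents; I assume 0.3 to 0.9. The outcome SD is set to 1 at both occasions.

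**Step 1: what two occasions can identify.** Code time as 0 and 1. With random intercept variance a, slope variance b, covariance k and residual variance e, the observable moments are:

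- Var(baseline) = a + e
- Cov(baseline, 12 months) = a + k
- Var(12 months) = a + 2k + b + e

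These are three equations in four unknowns (rank 3), so b cannot be separated from e. With occasions at 0, 3, 6 and 12 months there are ten moments and the rank is 4, so for weight it can. Dropping the random slope leaves a model that fits two occasions, and the fixed group-by-time effect is estimable.

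**Step 2: variance of the group-by-time effect in the random-intercept HLM.** With baseline as a response and participants lost to follow-up contributing their baselines:

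Var(HLM) = 2 × [(1 − rho²)/c + (1 − rho)²/n]

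With complete data (c = n) this becomes 4(1 − rho)/n, the variance of a difference in mean change. At rho = 0.5 and n = 35 it is 4 × 0.5/35 = 0.0571, SE 0.239, the same as for change scores.

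**Step 3: variance with baseline adjustment.**

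Var(ANCOVA) = 2 × (1 − rho²)/c, times about 1 + 1/(2c − 4) for estimating one covariate.

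The mixed model with baseline means constrained equal has the same large-sample SE (for example 0.245 for both at rho = 0.5 with c = 25).

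**Step 4: worked case, rho = 0.5 with loss.**

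- HLM: 2 × (0.75/25 + 0.25/35) = 2 × (0.0300 + 0.00714) = 0.0743, SE 0.273
- ANCOVA: 2 × 0.75/25 = 0.0600; times 1 + 1/46 gives 0.0613, SE 0.248
- Ratio: 0.0613/0.0743 = 0.825

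**Step 5: the range.** Ratio of the ANCOVA variance (small-sample cost included) to the HLM variance:

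| rho (assumed) | 35 per arm complete | 25 of 35 per arm retained |
|---|---|---|
| 0.3 | 0.66 | 0.74 |
| 0.5 | 0.76 | 0.83 |
| 0.7 | 0.86 | 0.91 |
| 0.8 | 0.91 | 0.95 |
| 0.9 | 0.96 | 0.985 |

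As an equivalent increase in participants with loss: 1/0.825 = 1.21, 1/0.907 = 1.10 and 1/0.985 = 1.015 at rho 0.5, 0.7 and 0.9, that is about 21 %, 10 % and 1.5 %.

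**Dependence on n.** The Sample size section says 70 in each group, where other sections give 35. Apart from the small-sample factor, the ratio depends only on rho and the fraction retained, so this discrepancy hardly matters here: at rho = 0.5 the ratio without that factor is 0.0600/0.0743 = 0.81 for either size.

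**The case against.** The strongest reply has four parts.

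- **No growth model is fixed.** A reader might infer from the stated rationale that a random-slope model is planned and hence that the analysis cannot be carried out for blood and diet outcomes. The documents do not support this. They fix a two-level structure and say what such models can do; they specify no random slope. A random-intercept HLM meets the description and estimates the between-group comparison that the Outcomes section asks for. This part stands in full.

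- **This is analysis-plan detail.** Random effects and baseline handling are often left to a full protocol or SAP, neither of which is shown. This lowers the severity. It does not remove the point, because the article does name the model, puts the repeated measures at level 1 and sets the covariate rule; followed as written, these lead to a change-type contrast.

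- **Baseline adjustment is not excluded.** The p < 0.30 rule neither names nor bars the baseline value. If the screen were run against the 12-month value, it would readily pass: at rho = 0.5 with 50 completers, t = 0.5 × √48/√0.75 = 4.0. But the article does not say what the bivariate test relates the covariate to, or whether the baseline value is a candidate. If baseline is already a level-1 response, adding it as a covariate is not ANCOVA. So adjustment is possible but not ensured.

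- **The gain can be overstated.** A reader might use the textbook ratio (1 + rho)/2, which gives 0.75, 0.85 and 0.95 at rho 0.5, 0.7 and 0.9. That compares ANCOVA with change scores in completers. The planned HLM also uses the baselines of participants who are lost, so with 30 % loss the gain is smaller, as tabulated, and at high rho it nearly vanishes. This stands.

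**Conclusion.** The point holds as a low-severity improvement. The planned model is workable for the two-occasion outcomes and no bias in the treatment effect is shown. What is lost is precision: for rho from 0.9 down to 0.3, baseline adjustment lowers the variance by about 4 % to 34 % with complete data and by about 1.5 % to 26 % with about 30 % loss. These figures rest on an assumed rho, equal variances at the two occasions, equal loss in the arms, and baseline entering the HLM as a response without a constraint on its means.

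Only secondary outcomes are concerned: glucose, lipids, GPT and diet. The primary outcome, weight, has at least four occasions, and the sample size rests on weight alone. It would also be too strong to call the change free of any cost: ANCOVA spends one degree of freedom, and a completers-only ANCOVA discards the baselines of those lost.

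**What to change.** Add a sentence to Statistical analysis: continuous outcomes measured only at baseline and 12 months are analysed with prespecified adjustment for the outcome's baseline value, whatever the p < 0.30 screen shows. Two forms would serve:

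- a two-level mixed model with baseline means constrained equal across arms, which stays within the HLM framework and keeps the baselines of participants lost to follow-up, in line with intention to treat; or
- ANCOVA of the 12-month value on group and baseline value.

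Name one of them. State also that where baseline is used as a covariate, it is not at the same time a level-1 response. The sentence should be limited to continuous outcomes, because the article does not show that dietary pattern is a single continuous variable; the estimated daily energy intake is one. The individual-change rationale can be kept for outcomes with three or more measurements.

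The cost is one sentence and one degree of freedom per model, with no new data.

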### Screening and randomization

During the recruitment period, and until the calculated sample size has been achieved, participating primary care doctors and nurses who see patients aged 18 and older, for any reason, meeting the study definition of overweight or obesity will invite the patient to participate in the study (Fig. 1: Participant Flowchart). If the patient does not meet any exclusion criteria and agrees to participate, the health professional will schedule a primary care visit with a doctor or nurse participating in the study (**Visit 0**, screening) within about a week.

During the screening visit, eligible participants will be assigned a participation code. The randomization unit will be the individual patient, assigned 1:1 to the experimental or control groups. An independent investigator will be responsible for generating the allocation sequence using non-commercial Epidat 3.0 software. During this same visit, all participants will begin the standard diet intervention. In addition, **experimental group participants** will download the free app, receive a bracelet monitor (wearable device), and learn to use them (along with take-home instructions).

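### Centre is a known design factor in this two-centre trial, but the stated model leaves it out unless it happens to pass a p < 0.30 screen

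*Protocol article*

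**What the plan says.** The Participants and settings section of the protocol article says that the patients "will be recruited from two primary healthcare centres in the city of Tarragona and surrounding areas". Under Screening and randomization, "The randomization unit will be the individual patient, assigned 1:1 to the experimental or control groups". An independent investigator generates the sequence in Epidat, and the article does not say whether it is stratified.

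Both arms receive the same diet programme from participating doctors and nurses, and the Standard diet intervention section notes that "health professionals individualize the messages based on each person".

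The Statistical analysis section describes a hierarchical linear model, "presented as a 2-level hierarchical structure: level-1 units consist of the repeated measures for each subject, and level-2 units will be the subject". It admits covariates by a bivariate significance screen at p < 0.30. Centre is not named there, nor among the variables listed under Data collection.

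The Discussion section says "Randomization of patients to study groups will help to achieve a balance in sociodemographic and anthropometric characteristics" and adds that potential confounders will be handled by multivariate analysis.

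**The concern.** The two-level structure is a positive specification, not a gap that a condensed article leaves open. It covers visits within patient and nothing above the patient. Centre is known before the first patient is enrolled, and weight loss may differ between centres through case mix or delivery. Under the stated rule, centre enters only if the trial's own data show an association at p < 0.30.

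Two things are at stake, both modest. First, if centre is left out, variance between centres stays in the error term although it could be removed. Second, if the arms differ by chance in centre mix, the unadjusted estimate carries part of the difference between centres. In addition, the content of the primary model is not fixed before the data are seen.

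**Working it through.** **Inputs from the Sample size section.** "Accepting an alpha risk of 0.05 and a beta risk of 0.2 in a two-sided test"; "a difference greater than or equal to 3.9 kg"; "The common standard deviation is assumed to be 4.826 kg"; loss to follow-up 30%. The Abstract and the Participants and settings section give 35 per arm, so completers per arm are 35 × 0.70 = 24.5.

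**Assumptions, not in the documents.** Centre explains 1, 5 or 10% of the variance in weight change (ICC 0.01, 0.05, 0.10). The two centres are equal in size. Allocation is not stratified by centre.

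**Reproducing the plan's sample size.** n per arm = 2 × [4.826 × (1.96 + 0.842) / 3.9]² = 24.04. Dividing by 0.70 gives 34.3, rounded up to 35. Rounding to 25 first gives 25 / 0.70 = 35.7, or 36. So 35 per arm and 70 in total are reproduced. The Sample size section words the 70 as a per-group figure, which these inputs do not reproduce. That is a separate matter to reconcile, and 35 per arm is used here.

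**Power without centre.** SE = 4.826 × √(2/24.5) = 1.379 kg. Power = Φ(3.9/1.379 − 1.96) = 0.807.

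**Power with centre always in the model.** The residual SD becomes 4.826 × √(1 − ICC):

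| ICC (assumed) | SE, kg | Power | n per arm before dropout |
|---|---|---|---|
| 0 (no gain) | 1.379 | 0.807 | 25 |
| 0.01 | 1.372 | 0.811 | 24 |
| 0.05 | 1.344 | 0.827 | 23 |
| 0.10 | 1.308 | 0.846 | 22 |

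These are normal approximations and ignore the one degree of freedom spent. They compare always adjusting with never adjusting. The p < 0.30 screen would admit centre in some data sets, more readily when the gap between centres is large, so the gain over the stated rule is, if anything, smaller.

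**Chance imbalance in centre mix.** With 70 patients, 35 from each centre and 35 per arm, the number X from one centre in the experimental arm is hypergeometric (70, 35, 35). The difference in centre share between arms is (2X − 35)/35, with standard deviation 0.120. A difference of 20 points or more means X ≤ 14 or X ≥ 21, with probability 0.151.

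**Size of the resulting shift.** For two equal centres whose mean losses differ by g, the between-centre variance is g²/4. Setting this equal to ICC × 4.826² gives g = 2 × 4.826 × √ICC. The shift at a 20-point imbalance is 0.20 × g:

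| ICC (assumed) | g, kg | Shift at 20 points, kg | Share of 3.9 kg | In units of SE 1.379 |
|---|---|---|---|---|
| 0.01 | 0.97 | 0.19 | 5% | 0.14 |
| 0.05 | 2.16 | 0.43 | 11% | 0.31 |
| 0.10 | 3.05 | 0.61 | 16% | 0.44 |

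At one standard deviation of imbalance (12 points) the shifts are 0.12, 0.26 and 0.37 kg.

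**The case against.** The strongest defence is that patients are randomised individually, so centre can differ between arms only by chance. The standard error of the unadjusted comparison already covers that variation, and the test is valid without a centre term. The likely shift is well under one standard error, the gain in power is a few points at most, and no ICC is given to show that it is even that. The plan also does not rely on randomisation alone, because the Discussion promises multivariate control. All of this stands, and it limits the point to precision and prespecification. It does not remove the point: the multivariate control described is the p < 0.30 rule, and that rule does not guarantee that centre is in the model.

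A reader might infer three stronger criticisms. The documents support none of them.

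- **Arm is confounded with the treating professional.** The screening visit is booked with a participating doctor or nurse before allocation, and the diet programme starts at that same visit. The article describes no reassignment of patients by arm and no subset of staff trained on the app. The 8 hours of training concern the standard diet intervention and aim to make delivery uniform. Who conducts the later visits is not stated, but silence does not show confounding.
- **The type I error is inflated.** That would need each professional to treat one arm only, together with a number of professionals and an ICC that appear nowhere in the article.
- **Allocation is unstratified.** The article does not say so. Strata and block sizes are details that a journal article commonly leaves to the full protocol.

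**Conclusion.** The point holds as a matter of precision and prespecification. The stated model omits centre and lets a significance screen decide whether it returns. If centre explains 1 to 10% of the variance, always including it raises power from 0.807 to between 0.811 and 0.846. It also removes a shift of 0.19 to 0.61 kg when centre mix differs by 20 points, an event of probability about 0.15. These sizes rest on an assumed ICC range, and the imbalance figures also assume equal centres and no stratification. If allocation is in fact stratified by centre, the imbalance part largely falls away, while the case for having centre in the model remains. The randomised comparison is valid either way.

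**What to change.** State in the Statistical analysis section that centre is a fixed effect in the model for weight change, always included and exempt from the p < 0.30 screen. Two centres are too few to estimate a random centre level, so a third level is not the remedy. If the model takes weight at each visit, with baseline among the responses, the centre term must act on change over time (centre by visit) to have this effect.

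The cost is one sentence of analysis text and one degree of freedom for a centre main effect in a model of change. A centre-by-visit term costs one for each modelled change. No new data are needed, because each patient's centre is known at recruitment.

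Optionally, record the treating professional at each visit so that a sensitivity analysis can examine a professional effect. This adds one field to the visit form and would need to be in place while visits are under way.
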